## Abstract

Peripheral arterial disease (PAD) commonly presents with intermittent claudication, for which supervised exercise therapy (SET) is recommended as first-line treatment; however, real-world SET non-completion is frequent and a clinically relevant subgroup of patients fails to achieve meaningful functional improvement. No validated pre-treatment tool currently identifies these likely non-responders. This protocol describes a prospective single-centre observational cohort study designed to determine whether body composition derived opportunistically from routine computed tomography angiography (CTA) at the third lumbar vertebral level (L3), specifically skeletal muscle density and visceral adipose tissue (VAT) area, independently predicts 3-month SET outcome in patients with Fontaine IIa–IIb intermittent claudication. A total of 128 consecutive patients will be enrolled at the Complex Cardiovascular Centre, Hospital AGEL Trinec-Podlesi, Czech Republic. The primary composite outcome is treatment success at 3 months, defined as both functional improvement on standardised treadmill testing, expressed as an absolute increase of at least 50 m or a relative increase of at least 50% in maximum walking distance (MWD), and freedom from revascularisation. Treatment failure includes SET non-completion, functional non-response among programme completers, or revascularisation during follow-up irrespective of functional result. Associations between skeletal muscle density, VAT area, and treatment outcome will be examined using prespecified multivariable logistic regression adjusted for age, sex, and baseline MWD, with bootstrap internal validation. As this is a study protocol, no outcome data are yet available; enrolment is planned to begin in June 2026. This study will assess whether zero-burden metabolic phenotyping from routine CTA can help identify patients less likely to benefit from conservative management alone, but any derived model will require external multicentre validation before clinical use. ClinicalTrials.gov: NCT07433309.

## Introduction

Peripheral arterial disease (PAD) affects approximately 236 million individuals aged 25 years and older, with intermittent claudication being its most common symptomatic manifestation [1]. International clinical practice guidelines, including the 2024 American College of Cardiology/American Heart Association (ACC/AHA), 2024 European Society of Cardiology (ESC), and 2024 European Society for Vascular Surgery (ESVS) guidelines, unanimously endorse supervised exercise therapy (SET) as the first-line treatment for intermittent claudication [2–4]. Furthermore, the 2024 ESC and ESVS guidelines specify that revascularization should be deferred until conservative management has been adequately trialed [3, 4]. A Cochrane systematic review demonstrates that exercise significantly enhances maximum walking distance and functional performance compared to no exercise [5]. Additionally, a second Cochrane review confirms the superiority of SET over home-based exercise and walking advice alone [6]. A meta-analysis of 15 randomized controlled trials shows significant improvements in physical health-related quality of life and perceived walking ability with structured exercise programs, although mental health component scores were not significantly affected [7].

Despite these benefits at the population level, individual treatment responses exhibit considerable heterogeneity. In the Invasive Revascularization or Not in Intermittent Claudication (IRONIC) study, 25% of conservatively managed patients ultimately required revascularization over five years, despite achieving comparable long-term outcomes to the revascularization group. This underscores both the tolerability of conservative management and the existence of a subgroup with insufficient response [8]. Real-world SET series report non-completion rates of 40–50% [9]. Conventional clinical predictors — including ankle-brachial index (ABI), age, sex, and disease severity — do not reliably forecast the extent of functional improvement achieved with SET [10]. However, patients with lower baseline walking capacity may derive proportionally greater benefits [10]. Currently, no validated metabolic tool exists to identify, prior to therapy initiation, patients lacking the biological substrate for aerobic adaptation, making them unlikely to benefit from a sustained exercise program.

Chronic lower-limb ischemia drives progressive skeletal muscle remodeling characterized by myofiber pathology, mitochondrial dysfunction, impaired oxidative phosphorylation, signs of denervation, and intramuscular lipid infiltration, which can be detected as reduced computed tomography (CT) attenuation [11, 12]. These tissue-level alterations directly constrain the capacity for aerobic adaptation — the primary mechanism through which SET exerts its functional benefits. CT-derived skeletal muscle attenuation in Hounsfield units (HU) correlates with histologically confirmed muscle lipid content [12]. At the L3 vertebral level, single-slice CT analysis provides whole-body composition estimates that are strongly correlated with dual-energy X-ray absorptiometry (DXA; *r* ═ 0.86–0.94) [13]. Visceral adipose tissue (VAT) functions as a systemic endocrine and pro-inflammatory compartment and is independently associated with insulin resistance, atherogenic dyslipidemia, and chronic systemic inflammation, potentially impairing exercise adaptation through mechanisms beyond the ischemic limb [14]. CT angiography (CTA) is routinely performed in symptomatic PAD patients being evaluated for revascularization [2, 15], making L3 body composition extraction a low-burden, opportunistic measurement. Our group has previously demonstrated that L3 CT-derived body composition parameters independently predict outcomes in patients undergoing transcatheter aortic valve implantation (TAVI) [16], and has developed a user-friendly clinical implementation tool based on this methodology [17], providing direct biological plausibility in a comparable cardiovascular rehabilitation context.

The primary aim of this study is to determine whether L3 CT-derived skeletal muscle density and VAT area independently predict composite SET treatment success at three months in patients with Fontaine IIa–IIb intermittent claudication. Two co-primary hypotheses are tested: H1 proposes that lower skeletal muscle density per 1 standard deviation (SD) decrease will predict treatment failure; H2 posits that higher VAT area per 1 SD increase will predict treatment failure. H3, which states that the sarcopenic obesity phenotype is associated with the lowest treatment success rates across body composition phenotype groups, is designated as a secondary/descriptive hypothesis and is not included in the family-wise Bonferroni correction for the co-primary analyses. This is a prospective observational derivation cohort study, hereafter referred to as CT Body Composition as Predictor of Exercise Therapy Outcome in PAD (COMPOSE-PAD); external multicenter validation is the pre-specified and required next step before clinical translation.

## Materials and methods

### Study design and setting

This is a prospective, single-center observational cohort study (COMPOSE-PAD) conducted at the Complex Cardiovascular Centre, Hospital AGEL Trinec-Podlesi, Trinec, Czech Republic. Enrollment is anticipated to commence in June 2026 and is planned to conclude in September 2030, with primary completion expected in December 2030 (three months after the anticipated last enrollment) and study completion expected in January 2031, with long-term follow-up ending in March 2032 (18 months after the last enrollment). Long-term outcomes, including major adverse limb events (MALE), major adverse cardiovascular events (MACE), and all-cause mortality, will be assessed retrospectively after the study’s completion in January 2031. This analysis will utilize national registry data and electronic health records. The study is reported in accordance with the Standard Protocol Items: Recommendations for Interventional Trials (SPIRIT) guideline [18]. The SPIRIT checklist is provided as a supplementary file. COMPOSE-PAD is prospectively registered as an observational cohort study at ClinicalTrials.gov (NCT07433309; study type: observational; time perspective: prospective). There is no randomization, no experimental treatment allocation, and no interventional comparator.

**Table 1 TB1:** Eligibility criteria for study enrollment

**Inclusion criteria**	**Exclusion criteria**
Age ≥18 years Confirmed PAD defined by at least one of: resting ABI ≤0.90; duplex ultrasonography demonstrating ≥50% stenosis in a relevant lower limb vessel; or CTA demonstrating hemodynamically significant stenosis (≥50% diameter reduction) in a named below-aortic vessel associated with the presenting claudication territory. MRA may serve as additional confirmatory diagnostic evidence for PAD diagnosis but does not substitute for CTA eligibility; patients with MRA-only imaging lacking an eligible diagnostic CTA are excluded. “Flow-limiting” disease is defined as haemodynamically significant stenosis (≥50% diameter reduction) in a named below-aortic vessel on CTA or duplex ultrasonography, associated with the presenting claudication territory. TASC II anatomical severity classification is recorded at baseline. Fontaine stage IIa or IIb intermittent claudication Scheduled for institutional SET program Existing CTA with an L3 axial slice suitable for body composition analysis, acquired within 12 months prior to enrollment. Where multiple eligible CTAs exist within the 12-month window, the most recent scan is used. Patients without an eligible CTA within this window are excluded. Capacity to provide written informed consent	Fontaine stage III or IV PAD (critical limb-threatening ischemia) Ipsilateral lower extremity revascularization within 6 months prior to enrolment Absolute contraindication to structured exercise (e.g., unstable cardiac disease, severe pulmonary hypertension, uncontrolled arrhythmia) Cognitive impairment (MMSE < 24) Active malignancy or systemic condition expected to substantially alter body composition independently of the intervention Estimated life expectancy <12 months, assessed by the enrolling physician based on terminal malignancy, end-stage organ failure, or documented palliative care status at screening

Abbreviations: ABI, ankle–brachial index; CTA, computed tomography angiography; L3, third lumbar vertebral level; MMSE, Mini-Mental State Examination; MRA, magnetic resonance angiography; PAD, peripheral arterial disease; SET, supervised exercise therapy; TASC II, TransAtlantic Inter-Society Consensus II.

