### Eligibility criteria

Eligibility criteria are outlined in Table 1. Briefly, inclusion requires participants to be aged ≥18 years, with confirmed PAD defined by at least one of the following: resting ABI ≤0.90, duplex ultrasonography demonstrating ≥50% stenosis in a relevant lower limb vessel, or CTA demonstrating hemodynamically significant stenosis (≥50% diameter reduction) in a named below-aortic vessel associated with the presenting claudication territory, classified according to the Trans-Atlantic Inter-Society Consensus II (TASC II) anatomical severity framework and recorded at baseline. Magnetic resonance angiography (MRA) may serve as additional confirmatory diagnostic evidence for PAD diagnosis but does not substitute for CTA eligibility; patients with MRA-only imaging lacking an eligible diagnostic CTA are excluded. Participants must have Fontaine stage IIa or IIb intermittent claudication, be scheduled to participate in the institutional SET program, and have a CTA with an axial slice at the L3 vertebral level suitable for body composition analysis, acquired within 12 months prior to enrollment (the most recent eligible scan is used when multiple CTAs are available). Capacity to provide written informed consent is required. Requiring an existing diagnostic CTA selects patients who have undergone revascularization workup; the implications for external validity of this referral selection are discussed in the Limitations section. Exclusion criteria include Fontaine stage III or IV PAD; ipsilateral revascularization within six months preceding enrollment; absolute contraindication to structured exercise; cognitive impairment (Mini-Mental State Examination score <24); active malignancy expected to alter body composition independently of the exercise intervention; and estimated life expectancy <12 months, defined as the enrolling physician’s clinical judgment regarding survival likelihood based on terminal malignancy, end-stage organ failure, or documented palliative care status at screening.

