Quality control procedures include verification that calcified plaque is excluded from the muscle compartment, flagging scans with an inter-compartment boundary coefficient of variation exceeding 35% for consensus adjudication by two independent analysts, and benchmarking inter-analyst agreement on the first 20 scans of the series prior to full enrollment. This is assessed using Bland-Altman analysis and the intraclass correlation coefficient (ICC). A pre-specified ICC threshold of ≥0.90 is required for both skeletal muscle density and VAT area before proceeding to full enrollment. If the ICC falls below 0.90 on the 20-scan benchmark, the segmentation protocol will be reviewed, and analysts retrained; an additional benchmark of 10 scans will be conducted before full enrollment begins. Baseline body composition (T0) is derived from existing diagnostic CTA scans, with the most recent scan selected when multiple eligible CTAs are available within a 12-month window. A standardization and inter-scanner variability policy will be documented prior to the first enrollment and applied throughout the multi-year enrollment period; any scanner upgrades or protocol changes will also be documented and assessed for their potential impact on HU consistency.

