Limitations must be stated with equal clarity. This is a single-center derivation cohort; generalizability to other health systems, exercise program models, and patient populations cannot be assumed. The L3 vertebral level does not directly capture ischemia-specific lower limb myopathology, and the biological distance between L3 and the affected musculature is acknowledged as a limitation rather than a design strength. No PAD-specific HU threshold for myosteatosis has been prospectively validated; the cohort-derived threshold established in this study is exploratory and hypothesis-generating (see sensitivity analyses #8 and #9 in Table 3 for assessment of alternative literature-derived values of 33 HU and 41 HU, respectively). AutoMATiCA was validated in oncology and critical care cohorts [20], but not in PAD; vascular calcification—highly prevalent in PAD—represents a specific source of measurement error: calcified plaque within or adjacent to the muscle compartment may not be fully excluded by the 150 HU ceiling, potentially inflating skeletal muscle density estimates; this systematic bias is specific to PAD imaging and is acknowledged as a limitation that cannot be fully quantified without PAD-specific validation data. The performance of the segmentation algorithm in the context of PAD-specific imaging protocols has not been independently established. The three-month primary endpoint may not capture delayed functional divergence between metabolic phenotype groups. The observational design precludes causal inference. The TASC II anatomical disease severity classification is recorded as a baseline variable and is included as a covariate in the expanded confounding model; however, as a potential confounder linking disease anatomical extent to both body composition phenotype and SET response, residual confounding by vascular disease extent cannot be fully excluded in a derivation cohort of this size. Requiring an existing diagnostic CTA introduces a selection bias: patients without prior CTA workup are excluded, meaning the cohort reflects those who have undergone imaging-based revascularization evaluation. Transportability to settings without routine CTA-based PAD workup or to patients managed without imaging evaluation cannot be assumed and necessitates specific consideration in external validation studies.

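### A 12-month CTA window with a 6-month ipsilateral revascularisation exclusion lets the only qualifying scan pre-date a procedure, so a treated lesion can confirm PAD and be graded for TASC II

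*Protocol article*

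**What the plan says.** Two look-back windows are set in Table 1 of the protocol article and repeated under Eligibility criteria.

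- **Imaging.** The patient must have an "Existing CTA with an L3 axial slice suitable for body composition analysis, acquired within 12 months prior to enrollment". If there are several, "Where multiple eligible CTAs exist within the 12-month window, the most recent scan is used".
- **Earlier procedures.** Table 1 excludes "Ipsilateral lower extremity revascularization within 6 months prior to enrolment"; the Eligibility criteria text gives the same limit as "ipsilateral revascularization within six months preceding enrollment". Contralateral procedures are not mentioned in either place.

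The CTA can serve three purposes.

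- **Confirming PAD.** ABI, duplex or CTA is each sufficient. The CTA route reads "or CTA demonstrating hemodynamically significant stenosis (≥50% diameter reduction) in a named below-aortic vessel associated with the presenting claudication territory" and has no date condition beyond the 12-month window.
- **Anatomical grading.** The Eligibility criteria text attaches TASC II to the imaged stenosis and has it recorded at baseline. It does not name the source scan. The Discussion says: "The TASC II anatomical disease severity classification is recorded as a baseline variable and is included as a covariate in the expanded confounding model".
- **Predictors.** Under CT body composition analysis: "Baseline body composition (T0) is derived from existing diagnostic CTA scans".

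**The concern.** The imaging window is twice as long as the procedure exclusion, and the two are not linked. The qualifying CTA can therefore have been taken before a revascularisation that the criteria tolerate. The most-recent-scan rule does not prevent this when the pre-procedure scan is the only one in the window.

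Two baseline items are then at stake. First, PAD can be confirmed by a stenosis that has since been treated, with no requirement to show that flow-limiting disease is present now. Second, TASC II may describe anatomy that no longer exists. TASC II is in the expanded model to test whether the body-composition associations are independent of disease extent, and the Discussion itself names it as a potential confounder. A grade taken before a procedure does that job less well.

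The limitations discuss selection through the requirement for a CTA. They do not discuss the timing of the scan relative to a procedure.

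**Working it through.** **Inputs**

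- CTA look-back: 12 months (Table 1; Eligibility criteria; CT body composition analysis).
- Ipsilateral revascularisation exclusion: 6 months (Table 1; Eligibility criteria).
- Contralateral exclusion: none stated.
- Planned enrolment: 128 (Sample size).
- Expanded model: about 12 predictors and 40 expected events (Statistical analysis).

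**Step 1. The plan's own enrolment figure.** It serves below only as a base for percentages. 100 / (1 − 0.22) = 128.2, and 128 × 0.78 = 99.8 evaluable, so 128 reproduces to within rounding. Nothing in this point changes it.

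**Step 2. Is the sequence admissible?** Let c be the months from CTA to enrolment and r the months from revascularisation to enrolment. The criteria require c ≤ 12 and, for the same leg, r > 6. The scan pre-dates the procedure when c > r. Together these give

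6 < r < c ≤ 12,

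an interval of 12 − 6 = 6 months. In whole months, r = 7, 8, 9, 10 and 11 allow 5, 4, 3, 2 and 1 values of c, so 15 combinations. One is c = 10, r = 8. These are possible timings, not patients.

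**Step 3. Contralateral procedures.** With no exclusion, any r < c ≤ 12 is allowed: 12 + 11 + … + 1 = 78 whole-month combinations. The consequence is weaker here, because the lesion in the presenting territory has not itself been treated. It could matter where the procedure or the TASC II grade takes in aorto-iliac anatomy, which the documents do not settle.

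**Step 4. Which changes close the gap?**

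| Change | Same-leg combinations left | Contralateral combinations left |
|---|---|---|
| None | 15 | 78 |
| Make the two windows equal | 0 | gap not closed |
| CTA must post-date the last lower-limb revascularisation | 0 | 0 |

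**Step 5. How many patients?** The documents give no share. As an assumption only, with 128 enrolled:

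| Assumed share | Patients |
|---|---|
| 2% | 2.6, about 3 |
| 5% | 6.4, about 6 |
| 10% | 12.8, about 13 |
| 20% | 25.6, about 26 |

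**Step 6. Which analyses does it reach?** The primary model contains muscle density, VAT area, age, sex and baseline MWD. TASC II is not among them. It enters only analysis #14, where 40 / 12 = 3.3 events per variable, in line with the stated 3 to 4.

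**The case against.** The best case on the other side concerns frequency and consequence, since the sequence itself is plainly allowed.

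**Frequency.** A reader might infer that the sequence is common because the article describes CTA as part of revascularisation workup. The documents do not support that: a workup need not lead to a procedure. These patients are scheduled for SET, which the Introduction presents as first-line with revascularisation deferred. An exposed patient needs a CTA, a later procedure inside the window, residual or renewed Fontaine II symptoms and no newer scan. Renewed symptoms may themselves bring a new CTA, which the most-recent-scan rule would select. This stands.

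**PAD confirmation.** CTA is one of three routes, the stenosis must belong to the presenting territory, and current claudication is required separately. A patient who claudicates again after treatment is unlikely to be free of PAD. This narrows the gap without closing it, because the rule as written still accepts a treated lesion as the sole evidence.

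**Body composition.** A reader might infer that pre-procedure scans bias H1 and H2. The article describes the L3 measures as systemic rather than limb-specific, and nothing in it shows that a limb procedure shifts them. A scan up to 12 months old is possible for any participant and is a separate matter.

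**TASC II.** A reader might infer that every such patient carries an obsolete grade, or that the error is differential with respect to outcome. The source scan is not fixed, so later imaging could be used, and no link between the error and SET outcome is shown. Model #14 is already labelled a robustness analysis to be read cautiously, and residual confounding by disease extent is acknowledged.

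**Missing detail.** A full protocol or imaging manual might name the scan used for TASC II. The two eligibility windows, however, are stated in full in the article, and followed exactly they admit these patients.

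**Conclusion.** The point holds as a minor eligibility gap. The criteria as written admit patients whose only qualifying CTA pre-dates a revascularisation: by up to 6 months for the same leg, and at any time in the 12-month window for the other leg. In those patients a treated lesion can be the sole confirmation of PAD. TASC II, if graded from that CTA, describes superseded anatomy in analysis #14.

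The admissibility of the sequence follows directly from the text. Its frequency does not: the 3 to 26 patients shown for 2% to 20% are illustrations and may overstate a small number. The effect on TASC II further assumes that the grade is taken from the qualifying CTA, which is the natural reading but is not stated. The documents do not support a claim that H1 or H2 is biased, and no sample-size, power or primary-endpoint figure changes.

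**What to change.** Add one clause to the CTA criterion in Table 1 and to the matching Eligibility criteria text: the scan must be no more than 12 months old at enrolment and must post-date the most recent lower-limb (including aorto-iliac) revascularisation. This covers PAD confirmation by CTA, TASC II grading from CTA and the T0 body composition together, and works for either leg. Imaging other than CTA that is used to confirm PAD or grade TASC II should meet the same date condition. Making the two windows equal would be a weaker repair, because it leaves contralateral procedures uncovered.

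If the sponsor prefers to keep these patients for their L3 measurements:

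- confirm PAD by an ABI or duplex obtained after the procedure;
- grade TASC II only from post-procedure imaging and otherwise set it to missing, to be imputed in the existing MICE model, which already includes the expanded-model covariates;
- flag these patients in the database so that their number can be reported.

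Under the first option a few previously revascularised patients become ineligible. Under the second a few have an imputed TASC II grade in one robustness analysis. Enrolment is planned to open in June 2026. Before then the change is a single clause; afterwards an outdated grade cannot readily be repaired.
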